#### **5.2.1.1      mRNA production**

Endogenous production of the expected mRNA will be assessed at the Prosensa laboratory in muscle tissue collected via the muscle biopsy.

For analytical methods refer to Appendix 4.

#### **5.2.1.2      Dystrophin expression**

Dystrophin expression will be assessed at the Prosensa laboratory in the muscle biopsies by immunofluorescence analyses of cross-sections and by western blot analyses of total protein extracts.

For analytical methods refer to Appendix 4.

#### **5.2.1.3      PRO051 level**

PRO051 levels in muscle tissue will be assessed at the Prosensa laboratory in the left-over material from the muscle biopsy after the results have been obtained for the mRNA production and dystrophin expression in the muscle tissue.

For analytical methods refer to Appendix 4.

### **5.2.2      mRNA production in peripheral blood mononuclear cells**

Whole blood samples (4 ml) will be collected into EDTA tubes at visit 2, 3, 5, 7 and 8 to assess exon skipping in mononuclear blood cells. The blood samples should be stored at room temperature and sent at room temperature to Prosensa Laboratory within 24 hours by courier mail.

For analytical methods refer to Appendix 4.

## **5.2.3 Muscle function**

### **5.2.3.1 Timed tests**

The timed tests consist of 10-meter walk/run test, timed rising from floor and stair climb. This combination of tests will be performed at visit 1, visit 1a, visit 2, visit 3, visit 4, visit 5, visit 6, visit 7, visit 8, visit 10 and visit 12.

#### ***10-Meter walk/run test***

The subject will be asked to traverse a marked 10-meter measured walkway as quickly as he safely can. The 10-meter walk/run test should be performed preferably barefoot without shoes or orthoses. If not possible, testing can be done with shoes/orthoses and any use of shoes/orthoses should be documented. Time is recorded with stop watch from when his first foot crosses the start line till when the second foot crosses the finish line. If wall is touched, it should be noted how often. Care needs to be taken to ensure that the patient is safe when completing this test. The assessor can walk nearby to provide 'emergency' help should it be needed, but must not support or provide manual assistance for the patient in any way.

#### ***Timed rising from floor***

The subject will be told to stand up as quickly as possible from supine position with his arms by his side. The patient is allowed to use his arms for support while rising from the floor. Time is recorded with a stopwatch from the initiation of movement until the assumption of upright standing. The area should be free from furniture and the patient should not be wearing orthoses or using any aids.

#### ***Stair climb***

The subject will need to ascend four steps. Time is recorded with a stopwatch from the initiation of movement until the subject stands on the fourth step. If a flight of steps with handrail is available these should be used. If not, a box step (approximately 15cm high) should be used. A plinth or other immovable object may need to be available to provide support.

## **5.2.4 6-Minute walk test**

Subjects will be requested to walk for 6-minutes at visit 1, visit 8 and visit 12. The subject will be asked to walk at his own preferred speed up and down the fixed distance of 25 meters until they are told to stop after 6 minutes. The test should be performed preferably barefoot and without aid. If not possible, testing can be done with shoes/orthoses/aid and any use of shoes/orthoses/aid should be documented. The subjects are warned of the time and are told that they may stop earlier if they feel unable to continue. The total distance walked within 6 minutes (or until the subjects stopped in case of early termination of the test) will be collected in meters.

## **5.2.5 Muscle strength**

### **5.2.5.1 Quantitative Muscle Testing (QMT)**

Quantitative muscle testing including spirometry will be performed visit 1, visit 1a, visit 2, visit 3, visit 4, visit 5, visit 6, visit 7, visit 8, visit 10 and visit 12, using the CINRG Quantitative Measuring System (CQMS).

### **5.2.5.2 Manual Muscle Testing (MMT)**

Manual muscle testing will be assessed at visit 1, visit 8 and visit 12. The Medical Research Council Scale is composed of a rating of 0-5 assigned to each muscle group tested. The Medical Research Council Scale has been modified and formalized to account for more grades of muscle weakness using a plus or minus designation (see Table 3).

*Table 3. Manual Muscle testing using a modified Medical Research Council Scale.*

| Grade | Description                                                                                                                                                                                                                           |
|--------------|----------------------------------------------------------------------------------------------------------------------------------------------------------------------------------------------------------------------------------------------|
| 5            | Normal strength                                                                                                                                                                                                                              |
| 5-           | Barely detectable weakness                                                                                                                                                                                                                   |
| 4+           | Muscle is weak, but moves the joint against a combination of gravity and mod-to-max resistance                                                                                                                                               |
| 4            | Muscle is weak, but moves the joint against a combination of gravity and moderate resistance                                                                                                                                                 |
| 4-           | Muscle is weak, but moves the joint against a combination of gravity and minimal resistance                                                                                                                                                  |
| 3+           | Joint is moved against gravity and a small amount of resistance. Muscle is capable of transient resistance but collapses abruptly. Not to be used for muscles capable of sustained resistance throughout the whole range of movement. |
| 3            | Joint is moved through the full available range of motion against gravity but cannot accept resistance.                                                                                                                               |
| 3-           | Joint is moved against gravity but not through the full available range of motion.                                                                                                                                                           |
| 2            | Joint is moved when the affects of gravity are minimized with a position change.                                                                                                                                                             |
| 1            | A flicker of activity is seen or palpated in the muscle.                                                                                                                                                                                     |
| 0            | No palpable muscle activity.                                                                                                                                                                                                                 |

## 5.3 Safety parameters during study period

### 5.3.1 Physical examination

A full physical examination will be carried out at visit 1, visit 2, visit 3, visit 4, visit 5, visit 6, visit 8, visit 10 and visit 12. The following body systems will be examined: general appearance; ear, nose, throat; cardiovascular; pulmonary; gastrointestinal; urogenital; nervous system; musculoskeletal; extremities; other. In addition, weight, height and Body Mass Index will be assessed at visit 1, visit 8 (day 43) and visit 12 (day 120).

### 5.3.2 Vital signs

At visit 1, visit 2, visit 3, visit 4, visit 5, visit 6, visit 7, visit 8, visit 10 and visit 12, systolic and diastolic blood pressure, pulse rate and respiratory rate will be recorded after five minutes rest in semi-recumbent position. At visit 2, visit 3, visit 4, visit 5 and visit 6 the measurements will be done at the time points indicated in Table 5 (Appendix 2).

Measures of blood pressure will be made using an automatic device. The same equipment will be used throughout the trial. Measurements will always be performed at the same arm.

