| Prolongation of aPTT
(due to protein binding in plasma)                                                                                                                | Transient prolongation related to plasma level (no signs of increased bleeding or bruising)                                                     |
| Activation of the alternative complement pathway in monkeys                                                                                                               | Not clinically significant in man                                                                                                               |
| Renal tubular changes: granules and degeneration/regeneration (highest steady state tissue levels)                                                                        | No renal effects observed to date                                                                                                               |
| Pro-inflammatory effects
- systemic primarily in rodents
- site of administration in monkeys (cytokine release after activation of monocyte and/or dendritic cells) | Fever and chills at high doses or rapid infusion rates (especially for unmodified phosphorothioate oligonucleotides)
Injection site erythema |
| Thrombocytopenia
(sequestration)                                                                                                                                       | Occasionally observed (sequence dependent & predicted by monkeys)                                                                               |
| Liver has the largest amount and second highest tissue levels of oligonucleotides
Mild ALAT/ASAT increase in mice related to pro-inflammatory effects                  | Elevations in serum transaminases or other signs of hepatotoxicity largely absent. Incidental findings with likely alternative causes.          |

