administration at 4 mg/kg/wk. It has been demonstrated for oligonucleotides that the pharmacokinetics between species extrapolates on the basis of body weight, rather than body surface area. Therefore, a species conversion factor is not required for calculating the starting dose in humans and this exception has been acknowledged in a FDA draft guidance document on estimating the maximum safe starting dose (FDA, 2005). In the previous clinical study, 0.8 mg (0.013-0.024 mg/kg) has been administered intramuscularly. The proposed dose level range for this study is 0.5-10 mg/kg/wk by subcutaneous administration. For the starting dose, this provides a safety margin of 35x compared to the NOAEL in monkeys and mice and 8x to in rats. These safety margins are considered appropriate and conservative, because (i) monkeys are considered more relevant than rodents, in particular the absolute pro-inflammatory effects in rodents have been less relevant for predicting dose limiting toxicities in humans for oligonucleotides; (ii) the subchronic monkey and mouse more closely mimic the intended clinical study in route and frequency of administration and duration of treatment; (iii) no test-item related systemic adverse event has been observed in the previous clinical study and a safety margin of >10x compared to the monkey NOAEL, the most relevant species, is considered sufficiently appropriate for a study in this population (DMD patients of 5-16 years).

Based on preliminary plasma pharmacokinetic data and non-compartmental analysis in monkeys, the maximum plasma concentration should remain below 150 µg/ml to limit acute effects. The AUC0-7d is approximately 920 µg.h/ml based on the NOAEL of 18 mg/kg/wk. In the proposed clinical study employing subcutaneous administration, the maximum dose of 10 mg/kg is expected to yield plasma peak concentration of approximately 50 µg/ml and an AUC0-7d of approximately 511 µg.h/ml.

Local reactions to subcutaneous injection (up to 250 mg) during the clinical study may occur, but these are not expected to be dose limiting. Past experience, especially with the first generation phosphorothioate oligonucleotides, indicate that fever and chills may be dose limiting toxicities. These reactions have been dose dependent, transient and well treatable.

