## 3 Study design

### 3.1 Overall study design

This study has been designed as an open label, multiple dose, escalating dose study. Depending on the MTD level, twelve to eighteen patients will be studied in four groups.

The study flow chart in Figure 3 outlines the dose escalation design of this study. Patients in the first group will receive 0.5 mg/kg, in the second group maximally 2 mg/kg, in the third group maximally 6 mg/kg and in the fourth group maximally 10 mg/kg.

[figure not shown]

Figure 3. Study flow chart with maximum dose levels to be administered.

Patients will receive one dose of PRO051 per week for 5 weeks. Each group will initially consist of 3 patients. Interim safety review for dose escalation will take place after review of all safety data that have been collected from at least up to and including the first three administrations of study medication (i.e. at least up to and including visit 4) for each patient and no prohibitive adverse events have been observed. In case of potentially dose limiting toxicity (DLT) in one of three patients in one group, this group will be expanded to six patients. In case of similar dose limiting toxicity in two or more patients, the inclusion of patients will be stopped at that dose level. Further, it will be decided if inclusion of new subjects should be stopped, or if the study should continue with a new lower dose group, or if the study should continue by expanding the previous group to six subjects. The dose level of the group which has a dose level one step below the group with similar dose limiting toxicity in two or more patients, will be considered the maximum tolerated dose (MTD).

The decision model for discontinuation or modification of dose escalation schedule is shown in Table 2.

Given the limited number of patients affected by DMD correctable by exon 51 skipping, an adaptive design was chosen to ensure that at least at the highest dose levels a reasonable number of patients could be included and that sufficient data on dose limiting toxicities could be collected. Furthermore, it was considered that the safety and tolerability profile warranting further investigations in a larger population could sufficiently be established with these group sizes.

No control group was included due to the limited number of patients available.

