#### **5.3.5      Adverse events**

The investigator will determine whether any AEs have occurred between visits. The subjects will be questioned using non leading questions and no specific symptoms will be suggested. Refer to Section 7 for further information on adverse event reporting.

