#### **5.3.6      Local tolerability**

Local tolerability at the injection site(s) will be established by assessing the absence or presence and severity of erythema, edema, pain, increased temperature, induration and bruising on a scale of 0 to 3 where:

0= absent  
1= mild  
2= moderate  
3= severe

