| Concomitant medication          | x-----x           |     |                |                |                |                |                |                |                |                  | x                                     |

1. Baseline assessments will be done at time point 3 to 0 hours prior to dosing
2. The investigator will contact the subject/parent two days after release from the institute to enquiry about the health of the subject and to assess the adverse events and concomitant medication.
3. Vital signs include blood pressure, pulse and respiratory rate
4. At visit 2 (day 1) and visit 6 (day 29) only
5. At visit 2 (day 1) only
6. At visit 2 (day 1), visit 3 (day 8) and visit 5 (day 22) only
7. Optional
8. Timed tests consist of: 10-meter walk/run, rising from floor, stair climb
9. At visit 3 (day 8), visit 4 (day 16) and visit 5 (day 22) only

Table 6. Schedule of assessments for visits 13 – 37 (treatment beyond study period)

| Visit                                        | 13         | 14  | 15   | 16   | 17             | 18   | 19   | 20   | 21             | 22   | 23   | 24   | 25             | 26   | 27   | 28    | 29             | 30    | 31    | 32    | 33             | 34    | 35    | 36    | 37             | Withdrawal
prior to visit
37 |
|----------------------------------------------|------------------------|-----|------|------|----------------|------|------|------|----------------|------|------|------|----------------|------|------|-------|----------------|-------|-------|-------|----------------|-------|-------|-------|----------------|------------------------------------|
| Day (window ± 1 day)                         | d          | d+7 | d+14 | d+21 | d+28           | d+35 | d+42 | d+49 | d+56           | d+63 | d+70 | d+77 | d+84           | d+91 | d+98 | d+105 | d+112          | d+119 | d+126 | d+133 | d+140          | d+147 | d+154 | d+161 | d+168          |                                    |
| Week                                         | w          | w+1 | w+2  | w+3  | w+4            | w+5  | w+6  | w+7  | w+8            | w+9  | w+10 | w+11 | w+12           | w+13 | w+14 | w+15  | w+16           | w+17  | w+18  | w+19  | w+20           | w+21  | w+22  | w+23  | w+24           |                                    |

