| Handheld myometry                            | x                      |     |      |      |                |      |      |      | x              |      |      |      | x              |      |      |       | x              |       |       |       | x              |       |       |       | x              |                                    |
| Spirometry                      | x                      |     |      |      |                |      |      |      | x              |      |      |      | x              |      |      |       | x              |       |       |       | x              |       |       |       | x              |                                    |
| Adverse events                               | x                      | x   | x    | x    | x              | x    | x    | x    | x              | x    | x    | x    | x              | x    | x    | x     | x              | x     | x     | x     | x              | x     | x     | x     | x              |                                    |
| Concomitant medication                       | x                      | x   | x    | x    | x              | x    | x    | x    | x              | x    | x    | x    | x              | x    | x    | x     | x              | x     | x     | x     | x              | x     | x     | x     | x              |                                    |
| Phone call / e-mail / SMS       | x                      | x   | x    | x    | x              | x    | x    | x    | x              | x    | x    | x    | x              | x    | x    | x     | x              |       |       |       |                |       |       |       |                |                                    |

1. Start of the treatment beyond study period will not be prior to patient and/or his parents, the investigator and the sponsor have all agreed that drug administration appears to improve the clinical status of the patient
2. To be completed prior to any other study procedure for the treatment beyond study period.
3. Other assessments to be performed prior to study medication administration unless specified otherwise

4. Vital signs include temperature, blood pressure, pulse and respiratory rate
5. Prior to study medication administration and at  $t = 3 \text{ hr} (\pm 15 \text{ min})$  after study medication administration

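### Fever may be dose limiting, but body temperature is not a scheduled measurement in the dose-escalation period

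*Protocol*

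**What the plan says.** Section 1.3.2 discusses which reactions might limit dose. It does not expect local injection reactions to do so, but says that past experience may "indicate that fever and chills may be dose limiting toxicities". Table 1 in the same section lists "Fever and chills at high doses or rapid infusion rates" as the clinical counterpart of the pro-inflammatory class effect.

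In the dose-escalation period, section 5.3.2 states that "systolic and diastolic blood pressure, pulse rate and respiratory rate will be recorded after five minutes rest in semi-recumbent position". Table 4 footnote 7 and Table 5 footnote 3 in Appendix 2 agree: "Vital signs include blood pressure, pulse and respiratory rate". The only temperature item in this period is in section 5.3.6, which scores the "absence or presence and severity of erythema, edema, pain, increased temperature, induration and bruising on a scale of 0 to 3"; that is a sign at the injection site.

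In the treatment-beyond-study period, the footnotes of Tables 6 to 14 read "Vital signs include temperature, blood pressure, pulse and respiratory rate", while section 5.6.2 again lists vital signs without temperature.

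The escalation rule in section 3.1 is "In case of potentially dose limiting toxicity (DLT) in one of three patients in one group, this group will be expanded to six patients"; Table 2 continues to the next dose at 0 of 3.

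**The concern.** Escalation, group expansion and the maximum tolerated dose (MTD) all follow from a count of DLTs in groups of three to six boys. Fever is one of the two reactions that section 1.3.2 singles out as possibly dose limiting. Yet a site that follows the schedule exactly takes no scheduled temperature in the phase where the count is made, and the extension tables schedule one where no escalation decision is made.

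Without scheduled readings, an absence of fever in the core data would mean that none was reported or noticed, which is weaker than saying that none was measured. No analysis plan can repair this later, because the data would not exist.

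**Working it through.** The protocol gives no fever rate, DLT rate or detection rate, so there is no stated figure to reproduce. The check compares passages, adds one count, and adds one illustration of direction.

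**1. Is temperature really absent?** Section 5.3.2, Table 4 footnote 7 and Table 5 footnote 3 give the same three measures, so this is not a broken table. The safety lists in the synopsis and in sections 3.3.5 and 8.5.6.2 do not name body temperature. The vital-sign summary in section 8.5.5.4 covers blood pressure and heart rate.

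**2. How else can fever be recorded?**
- Inpatient monitoring for about 30 hours after each dose (section 3.3.1).
- Physical examination at t=-3 h and t=24 h (Table 5).
- Adverse-event recording through the stay and at the 96-hour call (Table 5). On enquiry, section 5.3.5 says "The subjects will be questioned using non leading questions and no specific symptoms will be suggested".
- As an indirect laboratory marker, IL-6, TNF-α and MCP-1, but only at visits 2 and 6 (section 5.3.4.5). That leaves doses 2 and 3, inside the minimum review window, without this marker. C-reactive protein is not scheduled in Table 4.

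So fever can be captured, but through no scheduled measurement.

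**3. How many readings are affected?**
- Boys: 12 to 18 (section 4.1).
- Doses needed for the minimum escalation review: 3 (section 3.1).
- Post-dose vital-sign sets per dose: 3, at 3, 9 and 24 h (Table 5).
- 12 x 3 x 3 = 108 and 18 x 3 x 3 = 162 sets without a temperature.

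These are planned counts of readings and do not measure any effect on decisions. The fourth group has no planned higher dose, so its sets bear on the MTD and not on a further step.

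**4. Which way would an error go?** Let p be the true rate of dose-limiting fever at a dose, s the share recorded, and q = p x s. Under Table 2 the next dose is reached with 0 of 3, or with 1 of 3 followed by 0 of the next 3:

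P(escalate) = (1-q)^3 + 3q(1-q)^2 x (1-q)^3.

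Both p and s are assumptions. Boys are taken as independent and fever as the only DLT.

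| p | s = 1 | s = 0.75 | s = 0.5 | s = 0.25 |
|---|---|---|---|---|
| 0.10 | 0.906 | 0.944 | 0.973 | 0.993 |
| 0.20 | 0.709 | 0.814 | 0.906 | 0.973 |
| 0.33 | 0.434 | 0.605 | 0.783 | 0.933 |
| 0.50 | 0.172 | 0.351 | 0.600 | 0.862 |

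For example, at p = 0.20 and s = 0.5, q = 0.10 and P = 0.729 + 0.177 = 0.906. Under-recording always raises the chance of escalating. The table shows direction only; nothing in the protocol says which cell, if any, applies.

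**The case against.** The case on the other side is substantial.

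- **Fever is a possible DLT only.** Section 1.3.2 bases it mainly on first-generation compounds and calls the reactions transient and well treatable. Table 1 links them especially to unmodified compounds. PRO051 is chemically modified and given subcutaneously, a route that section 1.4 considers less prone to peak-level reactions. Section 1.3.2 reports no systemic immunostimulation in monkeys up to 140 mg/kg/wk. A reader might infer that the sponsor expected fever to limit dose; the text does not go that far. This stands.
- **Fever does not depend on a boy or parent volunteering it.** Boys are observed and examined at every dose, and section 7.1.1 counts an observed sign as an adverse event. Section 5.3.7 records the reason for each concomitant drug, so an antipyretic would leave a trace. The rule on non-leading questions governs enquiry, not observation. This also stands.
- **A dose-limiting fever in an observed inpatient is the least likely to be missed.** This is fair, and it is why the illustrative probabilities cannot be read as estimates. It does not remove the point. In the text at hand there is no definition or grade of a DLT, and whether a fever counts is a judgement that scheduled readings would inform. Incidental observation can also differ between staff and sites.
- **The core part is over.** Section 8.3 says that the monitoring committee was replaced after the core part was completed, and its text on the independent committee describes the period after escalation. A schedule change can no longer alter an escalation decision. This stands and redirects the remedy.

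**Conclusion.** The point holds in a limited form. The protocol names fever as a possible DLT but schedules no body temperature while DLTs are being counted. Ascertainment is unstandardised, and mild or transient fever can be missed. A missed fever makes the DLT count too low, never too high; the size of that error cannot be estimated from the protocol. The affected readings for the minimum review number 108 to 162, assuming the planned 12 to 18 boys.

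Two stronger readings are not supported. A reader might infer that the MTD is biased upward; that would require dose-limiting fevers to have been missed, and nothing shows this. A reader might also count every set at all five doses (12 x 5 x 4 = 240 to 18 x 5 x 4 = 360), but that includes pre-dose sets and doses 4 and 5, which the minimum review does not need.

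The conflict between section 5.6.2 and the footnotes of Tables 6 to 14 is a separate inconsistency in the extension.

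**What to change.** **In the plan:** add body temperature to the vital-sign definition in section 5.3.2, Table 4 footnote 7 and Table 5 footnote 3, at the existing time points. Add it to the vital-sign summary in section 8.5.5.4 and to the data reviewed before each escalation. The cost is one CRF field and a few seconds per set; no extra visit is needed.

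**Because the core part appears complete:** state in the core report that body temperature was not a scheduled measurement and that fever was ascertained through adverse-event reporting and clinical observation. The absence of recorded fever, and the MTD conclusion, should be read with that limit. The cost is a sentence or two.

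**For the extension:** reconcile section 5.6.2 with the footnotes of Tables 6 to 14, so that text and schedule define vital signs in the same way.
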